#### Urinary symptoms

Evaluated by the questionnaire Urogenital Distress Inventory (UDI-6); irritative symptoms, obstructive/discomfort and stress symptoms (range 0–18, higher score indicate higher disability) [18] and International Consultation on Incontinence Questionnaire Female Urinary Tract Symptoms Sex (ICIQ-FLUTSsex) for evaluation of female sexual matters associated with their lower urinary tract symptoms (range 0–14, higher values indicating increased symptom severity) [19].

#### Vaginal health index (VHI)

A gynecologic examination is performed by an experienced gynecologist at the baseline visit and at each follow-up visits using the VHI. VHI includes subjective scoring of moisture, fluid volume, epithelial integrity and elasticity and objective scoring of pH (VHI ranges 5–25, higher VHI scores indicate better health).

### Objective secondary outcomes

#### Change in vaginal pH

Vaginal pH is measured using pH-Indicator strips.

#### Change in vaginal histology

A punch biopsy of 4*4 mm is taken from the lateral left vaginal wall at the baseline visit and from the lateral right vaginal wall at the follow-up visit. The biopsy is immediately formalin fixated and then processed for light microscopy. Some sections are stained using haematoxylin and eosin (H&E), and others with Masson's trichrome stain and immunohistochemistry test. The biopsies are evaluated by a specialized gynecological pathologist at The Department of Pathology Randers Regional Hospital, reporting on the changes in the vaginal histology.

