## Methods

The VagLaser trial is a single-center study containing three sub-studies:I.A dose–response study exploring the optimal number of laser treatments needed to achieve an effect on GSM symptoms in BCS. A total of 30 participants will be included for a maximum of five treatments of vaginal laser therapy at 4–6 weeks' intervals.II.A randomized, participant blinded, placebo-controlled study to compare vaginal laser therapy with sham laser therapy in 60 BCS, with a fixed number of treatments. The number of vaginal laser treatments depends on results obtained from study I.III.A one-year follow up study on participants from study II. The participants from the active laser group will be offered a single "booster" treatment.

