### Data collection

Data are collected electronically and stored in Research Electronic Data Capture (REDCap, Aarhus University), which is a secure online database. Demographic characteristics are collected from women included at baseline visit as follows: age, BMI, smoking, parities, age at menopause, years since breast cancer diagnosis, years since start at endocrine therapy, type of endocrine therapy.Study I: Symptom data are collected at baseline, after each treatment visit and 6 months after the initial treatment. Vaginal biopsy is collected at baseline visit and 6 months after the initial treatment. Vaginal and urine microbiota are collected at baseline visit, at each treatment visit, and 6 months after initial treatment (Table 2).Study II: Symptom data, vaginal biopsy, vaginal and urine microbiota are collected at baseline visit and one month after the last treatment (Table 3).Study III: Symptom data, vaginal biopsy, vaginal and urine microbiota are collected at one year follow-up visit which is scheduled one year after the completion of the last treatment in the study II, and one month after the single "booster" treatment.

**Table 2 Tab2:** The timeline of the treatment protocol for study I is summarized

	**Baseline**	**Treatment no. 1**	**Treatment no. 2**	**Treatment no. 3**	**Treatment no. 4**	**Treatment no.5**	**4–6 weeks after 5.treatment**
**Timepoint (weeks/months)**	0 weeks	4 weeks	8 weeks	12 weeks	16 weeks	20 weeks	6 months
**Eligibility criteria**	x						
**Informed consent**	x						
**Information from the patient record**	x						
**Questionnaires**	x				x	x	x
**Gynaecological examination**	x		x	x	x	x	x
**Vaginal biopsy**	x						x
**Vaginal and urine Microbiota**	x		x	x	x	x	x

**Table 3 Tab3:** The timeline of the treatment protocol for study II is summarized

	**Baseline**	**Treatment no. 1**	**Treatment no. 2**	**Treatment no.3**	**Treatment no.4/no. 5**	**4–6 weeks after the last treatment**
**Timepoint (weeks/months)**	0	4 weeks	8 weeks	12 weeks	-	4 months
**Eligibility criteria**	x					
**Informed consent**	x					
**Information from the patient record**	x					
**Questionnaires**	x					x
**Gynaecological examination**	x					x
**Vaginal biopsy**	x					x
**Vaginal and urine Microbiota**	x			x	x	x

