### Randomization, blinding and informed consent

The women are e informed about the trial when they contact principal investigator. After signing of informed consent to participation, women are randomized in a 1:1 ratio to either laser group or sham group using an Internet-based randomization-program (REDCap, Aarhus University). Women are stratified by age, duration of prior endocrine treatment, and type of endocrine treatment. The participants in study II will be blinded to treatment allocation until the study has been completed.

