### Power calculation and statistical analysis

Considering the VAS score ranging for 0 to 10 for vaginal dryness as the primary outcome. In study one the sample size was calculated based on an expected mean 30% improvement on the VAS score for vaginal dryness from the third treatment compared to the fifth treatment. Aiming for a power of 90% and an alpha of 0.05 and a standard deviation of 2.9 was adopted [22], a sample size of 23 women were required. With an estimate loss of 20% participants during the five laser treatments, a total of 30 women will be included in study I. In study two the sample size was calculated based on an expected 30% improvement on the VAS score for vaginal dryness in the active laser group compared to the sham laser group. To achieve a power of 90% and an alpha of 0.05 with a standard deviation of 2.9 [22] it was determined that [22], a sample size of 21 women in each group was required. With an estimate loss of 20% participants during the second study, a total of 52 women will be included in study II, 26 in each group.

Statistical analyses will be performed using STATA. If the data followed a Gaussian distribution, the Student’s t-test will be used to test for differences between variable means. Otherwise, Mann Whitney's test will be used. For ordinal data from the questionnaires, Pearson’s χ^2^ and linear-by-linear tests will be performed. Paired test with one-way ANOVA will be used to evaluate change over time. Groups variables will be tested for change over time with two-way ANOVA (repeated measurements). A 2-sided *P*-value < 0.05 will be chosen as the level of statistically significance. Data are given as mean ± SD if they followed a Gaussian distribution; otherwise, median (range) are indicated.

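### Biopsy side is fixed by visit (left at baseline, right at follow-up), so uncontrolled before-after change in histology cannot be separated from any left-right difference between the vaginal walls

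*Protocol article*

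**What the plan says.** Change in vaginal histology is one of the objective secondary outcomes. Under that heading the protocol article states that the punch biopsy is "taken from the lateral left vaginal wall at the baseline visit and from the lateral right vaginal wall at the follow-up visit". The rule applies to all women, with no randomised or alternating order. The same paragraph continues: "The biopsies are evaluated by a specialized gynecological pathologist", with the task of "reporting on the changes in the vaginal histology".

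The Methods section describes Study I as a single group: "A total of 30 participants will be included for a maximum of five treatments of vaginal laser therapy". Under Data collection, each woman in Study I has two biopsies: "Vaginal biopsy is collected at baseline visit and 6 months after the initial treatment". Study II is "A randomized, participant blinded, placebo-controlled study to compare vaginal laser therapy with sham laser therapy in 60 BCS", with a biopsy at baseline and one about a month after the last treatment. The left-then-right rule makes no distinction between studies or arms.

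On analysis, the statistical section says "Paired test with one-way ANOVA will be used to evaluate change over time", and adds a two-way repeated-measures ANOVA for groups over time. It names no term for biopsy side. On blinding, the article states only that "The participants in study II will be blinded to treatment allocation until the study has been completed".

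**The concern.** When every woman is sampled on the left before treatment and on the right afterwards, visit and side are the same variable. If the walls differ systematically, the before-after contrast picks up that difference. The cause could be anatomy, or the way one operator angles the punch or reaches depth on each side. A paired test would then report it as a change over time.

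This matters most in Study I, where there is no control arm and the left-to-right contrast is the only histology contrast. It also affects any statement about change within one arm of Study II. The outcome at stake is secondary; the primary outcome, VAS vaginal dryness, is not touched.

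**Working it through.** The article states no sample size, effect size or SD for histology, so there is no figure of its own to reproduce. The check has two parts: what the design can identify, and an illustration of size.

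**1. Identifiability.** For woman *i*, let D_i be the follow-up value minus the baseline value, τ the change over time, δ the systematic right-minus-left difference, and e_i random error.

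- Fixed rule: D_i = τ + δ + e_i for every woman. The mean of D estimates τ + δ, and nothing in the data separates the two terms.
- Balanced order: D_i = τ + s_i·δ + e_i, with s_i = +1 if the left wall is sampled first and −1 if the right wall is first. With half in each order, the mean of D estimates τ, and the half-difference between the two order groups estimates δ.

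The design matrices confirm this:

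| Design | Columns | Rank |
|---|---|---|
| Study I, fixed rule (24 women + time + side) | 24 + 1 + 1 = 26 | 25 |
| Study I, side alternated | 26 | 26 |
| Study II, fixed rule (52 women + time + side + time-by-arm) | 52 + 1 + 1 + 1 = 55 | 54 |

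The single deficiency under the fixed rule is that the time and side columns are identical. In Study II the time-by-arm term is unaffected: (τ_laser + δ) − (τ_sham + δ) = τ_laser − τ_sham. The 52 comes from the sample-size section; using the 60 from the Methods section would not change the result.

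**2. Illustration of size in Study I.**

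Inputs: 30 women less the 20% loss in the power section gives 30 × 0.80 = 24 pairs. That loss was set for the VAS calculation and is borrowed here. The test is a two-sided paired t-test at 0.05, with τ = 0. The side difference d, in SDs of the paired differences, is **assumed**, because the documents give none.

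Formula: the rejection probability is P(|T| > t_crit), where T is noncentral t with n − 1 degrees of freedom and noncentrality d√n. For n = 24, √24 = 4.90, so d = 0.2 gives noncentrality 0.98 and d = 0.3 gives 1.47.

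| Assumed d | 24 pairs | 30 pairs (no loss) |
|---|---|---|
| 0 | 5.0% | 5.0% |
| 0.1 | 7.6% | 8.3% |
| 0.2 | 15.6% | 18.5% |
| 0.3 | 29.1% | 35.5% |

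The first row is as compatible with the documents as the others.

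**The case against.** Several points on the other side have force.

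- **Opposite walls are sensible.** They avoid sampling tissue that is healing from the first biopsy. This stands, and the fix keeps it; the weakness is the fixed order only.
- **The size is assumed.** There is no left-right difference, no histology SD and no numeric histology scale in the article, which describes stains and a pathologist's report. The error rates need a continuous score and a paired t-test. This stands, and the table shows only how the mechanism would act.
- **Study I is uncontrolled anyway.** Natural course, placebo response and use of the permitted cream would stay mixed with any laser effect after the sides are balanced. This stands. Balancing removes one avoidable component and does not make the study controlled.
- **The sham arm offers a benchmark.** It follows the same left-to-right rule, so its change shows roughly what side plus time give without active laser. This stands in part: the comparison is across studies, in different women and at different follow-up times, and it is not randomised.
- **It may be late.** Recruitment began on 16 February 2023, this version is dated 13 November 2023, and Study I comes first. Many baseline biopsies may already have been taken, though the article gives no count.

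Two stronger readings are tempting, but the documents do not support them. A reader might infer that the side label reveals the visit to the pathologist. The article does not say that side or visit is shown to the pathologist, and specimen coding is a detail a condensed article may leave to the full protocol. Only the conditional holds: if side is visible, the fixed order discloses the visit. In Study II that would not by itself disclose the arm.

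A reader might also count uneven lasering of the two walls as a side difference. That does not fit the argument. It would not be common to the laser and sham arms, so it would not cancel, and it could not produce a change where the laser has no effect.

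**Conclusion.** The point holds as a minor one about a secondary outcome. The stated sampling rule makes side and visit inseparable in Study I and in within-arm change in Study II. The between-arm histology comparison in Study II is sound in this respect, provided the side difference is anatomical or due to sampling and so is common to both arms.

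The bias equals the systematic left-right difference, which is unknown and may be zero. The 16% and 29% error rates depend on assumed side differences of 0.2 and 0.3 SD, 24 pairs and a continuous score; they are not estimates for this trial. What can be said firmly is that, under the fixed order, Study I's own data can neither show nor rule out such a difference.

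**What to change.** For women not yet sampled at baseline, in either study:

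1. Randomise or strictly alternate the side of the first biopsy.
2. Take the follow-up biopsy from the opposite wall.
3. Record the side at each visit and include it in the before-after histology comparison.

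For women already sampled under the present rule, state in the report that the Study I histological change is confounded with biopsy side, and give the same caution for any within-arm change in Study II.

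The cost is a sentence in the biopsy procedure and a side field in REDCap, with no extra biopsies, visits or staff. The downside is having to look up the earlier side at follow-up. The gain is limited to the side component.

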## Item from the World Health Organization trial registration data set

**Table Taba:** 

Data category	Information
Primary registry and trial identifying number	ClinicalTrials.gov: NCT06007027
Date of registration in primary registry	22 August, 2023
Primary sponsor	[name]
Secondary sponsors	[name] and [name]
Contact for public queries	[name], Mobile [name], Email [contact]
Contact for scientific queries	[name] Department of Obstetrics and Gynaecology, Randers Regional Hospital, Denmark Department of Clinical Medicine, Aarhus University, Denmark
Public title	Vaginal CO_2_ laser therapy for genitourinary syndrome in breast cancer survivors
Scientific title	Vaginal CO_2_ laser therapy for genitourinary syndrome in breast cancer survivors—A randomized blinded, placebo-controlled trial
Country of recruitment	Denmark
Health condition(s) or problem(s) studied	Genitourinary syndrome of menopause
Intervention(s)	Active comparator: SmartXIDE^2^V^2^LR, MonaLisa Touch, DEKA, Florence, Italy (Setting: dot power 30 W, dwell time 1000 μs, dot spacing 1000 μs and the smart stack parameter from 2–3) Placebo comparator: SmartXIDE^2^V^2^LR, MonaLisa Touch, DEKA, Florence, Italy (Setting: 0 W, dwell time 100 μs, dot spacing 2000 μs and the smart stack parameter from 1 to 1)
Key inclusion and exclusion criteria	Key inclusion criteria: Breast cancer survivor in endocrine therapy, age > 18 years, symptomatic genitourinary syndrome of menopause with vaginal discomfort and/or dyspareunia Key exclusion criteria: Use of non-hormonal/hormonal vaginal therapies (1 and 12 months prior to the baseline visit, respectively), treatment with Chemotherapy (6 months prior to the baseline visit)
Study type	Interventional Allocation: randomized Intervention model: parallel assignment Masking: blinded (participants) Primary purpose: reducing late effects of breast cancer treatment
Date of first enrolment	February 2023
Target sample size	90 participants
Recruitment status	Recruiting
Primary outcome	Vaginal dryness
Key secondary outcomes	Subjective outcomes are vaginal pain, itching, soreness, urinary symptoms and sexual function Objective outcomes are change in vaginal histology (punch biopsy), change in vaginal and urine microbiota and change in vaginal pH

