### Sham procedure used in the randomized study

Included patients are treated intravaginally with the fractional microablative CO_2_ laser system (SmartXIDE^2^V^2^LR, Monalisa Touch, DEKA, Florence, Italy), using the following settings: dot power 0.5 W, dwell time 100 μs, dot spacing 2000 μs and the smart stack parameter from 1 to 1. This procedure is identical to the treatment procedure and even the noise involved with firing the laser is maintained allowing blinding of the participants.

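### Masking is stated for participants only, so nothing in the document keeps the histology reader from knowing the arm in Study II or the visit in any sub-study

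*Protocol article*

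**What the plan says.** The masking level is stated in four places in the protocol article, always for the same party:

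- The WHO trial registration data set, under study type, has "Masking: blinded (participants", with no further role in the list.
- Methods describes Study II as "A randomized, participant blinded, placebo-controlled study to compare vaginal laser therapy with sham laser therapy in 60 BCS".
- The sham procedure section gives the purpose of the retained noise: "even the noise involved with firing the laser is maintained allowing blinding of the participants".
- The section on randomization, blinding and informed consent says "The participants in study II will be blinded to treatment allocation until the study has been completed".

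The histology section says "The biopsies are evaluated by a specialized gynecological pathologist" (in the pathology department of the trial hospital), with the task of "reporting on the changes in the vaginal histology". It fixes the sampling site by visit: "from the lateral left vaginal wall at the baseline visit and from the lateral right vaginal wall at the follow-up visit". It names the stains but no grading scale or measured quantity, and it does not mention coded slides, reading order or masking of the reader. The abstract, the registration data set and the objectives all class change in histology as an objective secondary outcome.

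**The concern.** A biopsy is objective material, but its reading is a judgement. Here the reader is asked to report change, with no scale in the document to limit that judgement. A reader who knows which women had active laser and expects remodelling may see more of it in that arm. The result would be a laser-sham difference in Study II without a difference in tissue.

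This matters because the Background explains the treatment by tissue remodelling, so histology is one of the outcomes that could support a biological effect apart from self-report. The Discussion also cites a sham-controlled study that found no statistically significant difference between the arms. A positive histology result here would carry weight, and it should not be open to the reply that the reader knew the arm.

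Knowledge of the visit is a second and weaker exposure. A specimen labelled with its side, or its date, shows whether it was taken at baseline or later. That can inflate apparent change over time in any of the sub-studies.

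**Working it through.** **Step 1. Is the reader covered by the stated masking?** The document gives no figure to reproduce, so the passages are set side by side.

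| Place in the article | Who is masked |
|---|---|
| Registration data set, masking entry | Participants |
| Methods, description of Study II | Participants |
| Sham procedure | Participants |
| Randomization, blinding and informed consent | Participants in Study II |
| Change in vaginal histology | Nobody mentioned |

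The four statements agree, and the pathologist falls outside all of them. No passage says that the pathologist knows the arm, and none says that the pathologist does not.

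**Step 2. What can each piece of knowledge do?**

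- *Arm known (Study II).* The reading can shift in one arm and not in the other. This can bias the laser-sham contrast.
- *Visit known only.* Left means baseline and right means follow-up in both arms alike. A reader who expects change may report more of it, but in both arms. Before/after readings are affected; the between-arm difference is not, by this route alone.

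**Step 3. How large could the effect of knowing the arm be?** The document gives no histology score, no SD and no estimate of reader bias. The following therefore rests on two assumptions: a continuous score compared by a two-sample t-test, and an arbitrary shift of b SD towards laser.

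Inputs from the section on power calculation and statistical analysis: two-sided alpha 0.05; 21 women per arm required, 26 per arm included.

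With no true effect, the test statistic follows a noncentral t distribution with

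- degrees of freedom = 2n − 2
- noncentrality δ = b × √(n/2)
- rejection rate = P(T > c) + P(T < −c), where c is the two-sided 5% critical value.

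For n = 21: df = 40, c = 2.021. With b = 0.3, δ = 0.3 × √10.5 = 0.972 and the rejection rate is 15.8%.

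For n = 26: df = 50, c = 2.009. With b = 0.3, δ = 0.3 × √13 = 1.082 and the rejection rate is 18.6%.

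| Assumed shift b | 21 per arm | 26 per arm |
|---|---|---|
| 0 SD | 5.0% | 5.0% |
| 0.2 SD | 9.7% | 10.9% |
| 0.3 SD | 15.8% | 18.6% |
| 0.5 SD | 35.3% | 42.4% |

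Methods gives 60 women for Study II, which is 60/2 = 30 per arm. At that size the rates for 0.2, 0.3 and 0.5 SD are 11.9%, 20.8% and 47.8%. A fixed reading bias does more harm as the trial grows, because the test becomes more sensitive to it.

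**The case against.** The strongest reply is that the harm depends on something the document does not state. Allocation is made in REDCap, treatment is given in Obstetrics and Gynecology, and slides are read in the Department of Pathology. The pathologist may never see the allocation. Slide coding and requisition labels are laboratory details that a journal article may leave to the full protocol.

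Part of this stands. A reader might infer that the biopsies are read with the arm known, and the documents do not support that. What remains is that the article does more than leave the matter out. It states the masking level, names participants alone each time, and gives an outcome it calls objective no protection under that statement.

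A reader might also infer that the left/right rule itself produces a spurious laser-sham difference. It does not. Side reveals visit, not arm, and it does so equally in both arms.

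Three further limits stand. The shift sizes and the continuous score in the calculation are assumptions, not findings about this trial. Histology is one of several secondary outcomes, and the primary outcome is a VAS completed by the participants themselves, who are masked in Study II. Lastly, coding cannot do everything: laser effects visible in the tissue may still give the arm away, and coding does not undo the fixed link between side and time.

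**Conclusion.** The point holds in this form: masking is stated for participants only, and nothing in the document prevents the histology reader from knowing the arm, which could bias the Study II comparison. Knowledge of the visit is a separate exposure that concerns before/after readings.

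The size of any bias is unknown. The rates of about 10% to 42% for shifts of 0.2 to 0.5 SD at 21 to 26 women per arm show how sensitive the comparison would be; they do not estimate what will happen. With no shift, the rate stays at 5%.

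The change is worth making because it is cheap and the outcome is presented as objective. It does not put the primary conclusion at risk. Confidence is medium, since slides may already be coded in practice; if they are, only the masking statement needs correcting.

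**What to change.** For biopsies not yet read:

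1. Send Study II slides to the pathologist under random codes that carry no arm, side, date or visit.
2. Read each woman's baseline and follow-up slides in random order. Reading in batches makes this possible, since the biopsies are formalin-fixed.
3. Release the codes only after the readings are locked, and derive change from the locked readings.
4. Mask Study I and Study III slides to visit in the same way. Study I has no control arm, and the Study III booster is offered only to the active group, so visit is what needs hiding there.
5. Change the masking entry to *participants and histology assessor*, and state from which biopsies the change applies.

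The cost is small: relabelling, and a delay until slides can be read in batches. No extra reader, biopsy or participant is needed, and sample size, power and alpha do not change. The report should say that coding reduces expectation bias but cannot hide visible laser effects in the tissue or separate side from time.
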